### Arms and interventions

#### Image-based prediction of stimulation settings

In the preparation of the *programming visit,* the preoperative MRI to localize deep brain nuclei and the postoperative CT to localize electrode placement will be analyzed by the computer algorithm. The software will then propose individual stimulation settings that yield high in silico potential for optimal antidystonic effect. Addressing efficacy and safety concerns we opted to define upper and lower boundaries for the amplitude range, which were derived in a data driven approach by using two standard deviations around the mean amplitude of the original cohort (mean = 3.4 mA, lower limit: 1.5 mA, upper limit: 5.5 mA) [10]. Having limits of 1.5 and 5.5 mA and a step size of 0.5 mA, there are 9 possible stimulation settings for each contact. The algorithm will check 4 heights representing 4 contacts, in case of directional electrode systems, these directional contacts will be used in ring-mode. This gives 4 × 9 for each side raised to the power of 2 for both hemispheres: 1296 possible combinations in total for each patient. These stimulator settings are than sorted by efficacy and filtered in a two step-manner. Firstly, the settings are removed if they share less than 50% overlap with the underlying model to maintain high confidence in the corresponding clinical efficacy. Secondly, outliers in the stimulation amplitude are excluded if the amplitude was one standard deviation above the average of the top 5 predictions. The proposed settings are checked for plausibility and safety by a DBS expert and saved on the stimulator as "computer"-program. For each stimulation side, one alternative stimulation setting will be proposed, in case the first option leads to otherwise not manageable side effects.

#### Clinical programming

The clinical programming will be performed by comprehensive reprogramming according to clinical best practices and represents the usual procedure for initial setting of the stimulator after surgery. This method and its exact algorithm have been published by Steigerwald and colleagues [11], and will only be briefly summarized here: the IPG is set as anode (+) and stimulation frequency and pulse width kept constant at 130 Hz and 120 μs, respectively. Than, each electrode is stimulated as monopolar cathode (−) by increasing the amplitude to a maximum of 6 V, as long as no adverse effects are elicited. The contact with the most beneficial effect is chosen for long-term stimulation. If no contact with acute beneficial effect can be determined, a contact that elicits phosphenes at an amplitude above 3 V was selected. If phosphenes are induced below 3 V, the next proximal electrode is chosen. The amplitude will be set to 0.5 V below the threshold of eliciting adverse. The resulting program is saved on the stimulator as "clinical"-program.

### Outcome measures

The primary efficacy endpoint is based on the blinded physician rating of dystonia severity reflected by Clinical Dystonia Rating Scales (BFMDRS or TWSTRS). The raters will be internationally recognized leading experts in the field of movement disorders that are not part of the study team or otherwise related to our center. For both interventions (best clinical settings and model predicted settings) we will calculate the symptom severity score after 4 weeks of continuous stimulation, expressed in percent of the pre-operative score. The primary endpoint is defined as “successful treatment with model predicted settings” (yes or no). The value is “yes” if the motor symptoms with model predicted settings are equal or better (tolerance 5% of absolute difference in percentages) to clinical settings.

Secondary endpoints will include measures of quality of life (SF-36 and CDQ24 questionnaire), calculated energy consumption of the neurostimulation system and physician time for programming. The study aims at estimating the success rate and explorative characterization of treatment failures in preparation for a confirmatory multicentre clinical trial.

#### Power calculation/sample size

The main conclusion from the success rate will be: (1) If the success rate is 80% or better, plan a superiority trial; (2) if the success rate is about 50%, plan an equivalence trial or, alternatively, examine the combination of best clinical practice and machine-based advice; (3) if the success rate is 20% or below, further exploratory work and considering other mathematical techniques is supported rather than a larger clinical trial. The data should be able to discriminate between these three scenarios in the sense that at most one of these three scenarios is in the 95% CI for the empirical success rates. This will be achieved with a sample size of n = 40 evaluable participants. A number of successes of 27 or more/14 to 26/13 or less does then rule out success rates of less than 50% / more than 80% or less than 20%/more than 50%, respectively, in the sense of the 95% CI.

We plan a data driven stopping if (1) 27 successes have occurred OR (2) at least 14 but no more than 26–k successes have occurred in 40–k patients for some number k = 1…12 OR (3) no more than 13–m successes have occurred in 40–m patients for some number m = 1…13, because it is then clear which two of the three rates 80%, 50% and 20% would be ruled out with 40 patients, regardless of the number of successes in the remaining patients. However, patients who have started their participation at this time should be able to complete the protocol.

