### Perspective

DIPS is the first randomized, double-blind and controlled comparison for computer-assisted DBS programming for patients with dystonia. The purpose of this study protocol is to answer the question of which programming method is more effective in controlling the symptoms of dystonia. If superiority or equality of computer-based prediction of optimal stimulation parameters can be shown, this would have significant consequences for dystonia patients worldwide, as their programming is currently still predominantly dependent on the experience of the DBS programmer. In silico objective testing of all possible stimulation parameters within seconds would save patients lengthy programming sessions and sometimes months of programming titration.

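### The 50% and 80% success-rate anchors ignore the one-sided 5-point tolerance, so a high rate supports non-inferiority within 5 points, not superiority

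*Protocol article*

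**What the plan says.** Under Outcome measures, each program is scored by the "symptom severity score after 4 weeks of continuous stimulation, expressed in percent of the pre-operative score". The model program succeeds in a patient if motor symptoms are "equal or better (tolerance 5% of absolute difference in percentages) to clinical settings". The tolerance is therefore 5 pp, and it is granted to the model program only.

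Under Power calculation/sample size, the success rate leads to one of three recommendations. The first two read: "If the success rate is 80% or better, plan a superiority trial; (2) if the success rate is about 50%, plan an equivalence trial". For the middle case, joining clinical programming with the software's suggestions is named as another option. The third reads: "if the success rate is 20% or below, further exploratory work".

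At most one of the rates 20%, 50% and 80% should lie inside the 95% confidence interval (CI): "This will be achieved with a sample size of n = 40 evaluable participants". The resulting zones are 27 or more, 14 to 26, and 13 or fewer successes, and the early-stopping rule uses the same counts. The Statistical analysis section gives advice on the next trial's hypothesis as the purpose of the primary analysis. The Perspective section says the study is to "answer the question of which programming method is more effective in controlling the symptoms of dystonia".

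**The concern.** Anchors of 50% for no difference and 80% for a clear advantage suit a plain better-or-worse comparison with no tolerance. Here patients who are tied or slightly worse on the model program also count as successes, which raises the rate for equal programs. The anchors were not moved to match.

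The recommendation on the next trial is the main product of this study. If the anchors are miscalibrated, two equal programs can point to a superiority trial, and a model program with a real deficit at the tolerance limit can land where the plan suggests an equivalence trial or a combined approach.

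**Working it through.** **1. The plan's own figures.** Exact two-sided (Clopper-Pearson) 95% CIs for x of 40:
- 13: 18.6% to 49.1%
- 14: 20.6% to 51.7%
- 26: 48.3% to 79.4%
- 27: 50.9% to 81.4%

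The cut-offs are right, and n = 40 meets the criterion that at most one of the three rates lies in the interval.

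**2. What the rate measures.** Let D be the severity on the model program minus that on the clinical program, in pp of the pre-operative score, so positive D means the model is worse. The success rate is P(D ≤ 5). For a continuous D:
- P(D ≤ 5) = 50% says that the median of D is +5, a median deficit of 5 pp. This holds for any SD and any shape.
- If the median of D is 0, then P(D ≤ 5) = 50% + P(0 < D ≤ 5). This exceeds 50% and approaches 100% as the spread of D shrinks.
- A CI wholly above 50% therefore rules out a median deficit of 5 pp or more. That is a non-inferiority statement with a 5-pp margin.

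**3. Size for equal programs.** The article gives no SD for D. Assumption: D is normal with mean 0 and SD s. Then p = Φ(5/s), and the number of successes is Binomial(40, p).

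| s (pp) | p = Φ(5/s) | P(≥27 of 40) | P(≥32 of 40, observed rate ≥80%) |
|---|---|---|---|
| 5 | 84% | 99.8% | 83% |
| 10 | 69% | 66% | 9% |
| 15 | 63% | 34% | 2% |
| 20 | 60% | 21% | 0.6% |

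If equality really gave 50%, P(≥27 of 40) would be 1.9%. The true rate under equality is exactly 80% at s = 5/0.8416 = 5.9 pp. The zone of 27 or more is the likelier result up to about s = 12 (50% there). Above that the middle zone is likelier (66% at s = 15, 79% at s = 20).

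**4. Sensitivity.**
- With a scaled t distribution (3 df) and the same SDs of 5 to 20, equal programs give 91% to 65%, so the normal assumption does not create the effect.
- A model program truly 2 pp worse has p = Φ(3/s). It reaches 27 or more in 82% of trials at s = 5 and 28% at s = 10.
- With a true median deficit of 5 pp (p = 50%), the count falls in the 14 to 26 zone in 96% of trials, since each outer zone has 1.9%.

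**The case against.** **The size rests on an unknown SD.** This is true. The nearest figure in the Introduction is the prediction error, 16.9 ± 11.6, with root mean square √(16.9² + 11.6²) = 20.5 pp. It is a different quantity. Used as the SD, it gives 60% success and a 20% chance of 27 or more, so the middle zone would be the usual result. A reader might infer that equal programs will generally be read as superior; the article does not support that. The meaning of a 50% rate, however, does not depend on the SD.

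**Superiority is tied to 80%, not to 27 of 40.** Literally so, and an observed 80% under equality is likely only below about SD 6. But the CI criterion and the first stopping condition treat 27 successes as leaving 80% as the only one of the three scenarios, so the lower count also matters.

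**The middle scenario also offers a combined approach.** That alternative is sensible when about half the patients do acceptably. The objection stands, and the criticism is confined to reading about 50% as equivalence.

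**The endpoint still says something about relative efficacy.** A reader might infer that the clinical program would score the same success rate against the model, so that the endpoint can show nothing about which is better. The first part needs D to be symmetric about zero. The second goes too far: 13 or fewer successes exclude 50% and so show a median deficit above 5 pp.

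**No paired motor estimate is listed.** A reader might count this as a gap. It is not a finding: the article is condensed, it refers to methods for paired data, and the analysis plan is not shown.

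**Conclusion.** The concern holds as a mismatch between the endpoint and the anchors. Two statements need no assumed SD: a true 50% rate marks a median 5-pp deficit rather than equivalence, and equal programs always exceed 50%. A high rate therefore supports non-inferiority within 5 pp and does not by itself point to superiority.

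The practical size does depend on an assumed normal paired difference with mean 0. Over SD 5 to 20 pp, the chance that equal programs land in the superiority zone is between about 11 times (21% against 1.9%) and about 50 times (99.8% against 1.9%) what it would be if equality meant 50%. Nothing is wrong with n = 40, the exact CI or the cut-offs as arithmetic. The point should be fixed, but it is not critical: the trial is exploratory, the CI remains valid, and the result is advice for planning rather than an efficacy claim.

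**What to change.** Keep the endpoint, the exact CI and n = 40, and change the reading:

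1. Describe the rate as the proportion of patients not worse than on clinical settings by more than 5 pp. Read a CI lying above 50% as support for a non-inferiority trial. Stop reading about 50% as equivalence.
2. Base the superiority or equivalence advice on the mean paired difference in percent of pre-operative score, with its 95% CI. Apply the rules in this order, so that they cannot overlap:
   - if the CI excludes 0 in favour of the model program: superiority;
   - otherwise, if it lies wholly within ±5 pp: equivalence;
   - otherwise: undetermined, with further exploratory work.

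   The order matters because a CI can both exclude 0 and lie within ±5 pp. At SD 5 with a true gain of 2.5 pp this happens in about 74% of trials.
3. Add the three-way split (better by more than 5 pp, within 5 pp, worse by more than 5 pp) as a descriptive companion.
4. State that the early-stopping counts settle only the success-rate statement, and that stopping early also makes the paired difference less precise. At 28 patients and SD 20 the half-width is 2.052 × 20/√28 = 7.8 pp.

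The cost is a rewritten scenario paragraph and two analyses of ratings already collected. The drawback is limited precision. At n = 40 the half-width is 2.023 × SD/√40, about 3.2 pp at SD 10 and 6.4 pp at SD 20. For truly equal programs the CI lies within ±5 pp in about 74% of trials at SD 10, 12% at SD 15 and 0.2% at SD 20. The advice will often be undetermined when the SD is large, and the plan should say so in advance.

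### The one-sided 5-point tolerance in the success definition does not fit the symmetric 80/50/20% anchors, so the advice on the next trial is biased and can be wrong

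*Protocol article*

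**What the plan says.** Protocol article, Outcome measures: severity after 4 weeks on each program is "expressed in percent of the pre-operative score", and treatment with the model settings is successful if "the motor symptoms with model predicted settings are equal or better (tolerance 5% of absolute difference in percentages" points, compared with the clinical settings. The tolerance works in the model's favour only.

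Power calculation/sample size ties three kinds of advice to the success rate:

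- "If the success rate is 80% or better, plan a superiority trial"
- "if the success rate is about 50%, plan an equivalence trial", or else study a combination of clinical practice and machine advice
- "if the success rate is 20% or below, further exploratory work" is supported rather than a larger trial

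The data are meant to leave at most one of these three rates inside the 95% CI. On that aim the protocol says: "This will be achieved with a sample size of n = 40 evaluable participants". The cut-offs are 27 or more, 14 to 26, and 13 or fewer successes. Recruitment may stop early once the final category is settled.

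Statistical analysis specifies the exact two-sided 95% CI. It gives advice on the hypothesis of the next, larger trial as the purpose of the primary analysis, and refers back to the sample size section for how that advice follows.

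**The concern.** Anchors and cut-offs that mirror each other about 50% suit an endpoint that gives 50% when the two programs are equal. This endpoint does not, because patients who are slightly worse on the model program also count as successes. The anchors are not adjusted for that.

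The advice is the declared product of the primary analysis, so a miscentred mapping affects what the study is for. Two errors are possible. Programs that hardly differ can be read as grounds for a superiority trial. A model program sitting at the tolerance limit can be read as grounds for an equivalence trial. A correct confidence interval prevents neither, since the rate is estimated properly and then read wrongly.

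**Working it through.** **Inputs.** Success rule and scale: Outcome measures. Anchors 80/50/20%, n = 40, cut-offs 27 and 13: Power calculation/sample size. Exact two-sided 95% CI: Statistical analysis. The SD of the within-patient difference is not stated, so 5 to 30 points is assumed as a range.

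**Step 1: the protocol's own figures.** Clopper-Pearson 95% limits at n = 40:

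| Successes | 95% CI |
|---|---|
| 27 | 50.9 to 81.4% |
| 26 | 48.3 to 79.4% |
| 14 | 20.6 to 51.7% |
| 13 | 18.6 to 49.1% |

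So 27 excludes 50%, 26 excludes 80%, 14 excludes 20% and 13 excludes 50%. For every count from 0 to 40, at most one anchor lies in the interval. The stated arithmetic reproduces.

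**Step 2: what a 50% rate means.** Let D be severity on the model program minus severity on the clinical program, in points of the pre-operative score (higher is worse). Success is D ≤ 5, so the success rate is P(D ≤ 5). If this is 0.5 and D is continuous, the median of D is +5: half of the patients are more than 5 points worse on the model program. No SD or distribution is needed. With X ~ Bin(40, 0.5), P(14 ≤ X ≤ 26) = 96.2%, so nearly all such trials fall in the middle category.

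**Step 3: what equal programs score.** If D is symmetric about 0, the success rate is 0.5 + P(0 < D ≤ 5). It exceeds 50% as soon as some patients differ by 5 points or less, and it rises as the programs become more alike.

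**Step 4: size.** Take D normal with mean 0. The success rate is p = Φ(5/SD), and X ~ Bin(40, p). Two readings of the superiority advice are shown: the category of 27 or more, where 80% is the only anchor the interval can still contain, and an observed rate of at least 80%, which is 32 of 40.

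| Assumed SD | p | P(X ≥ 27) | P(14 ≤ X ≤ 26) | P(X ≥ 32) |
|---|---|---|---|---|
| 5 | 84% | 99.8% | 0.2% | 83% |
| 10 | 69% | 66% | 34% | 9% |
| 15 | 63% | 34% | 66% | 1.7% |
| 20 | 60% | 21% | 79% | 0.6% |
| 30 | 57% | 11% | 89% | 0.2% |

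At a true rate of 50%, P(X ≥ 27) = 1.9%. Equal programs have an expected rate of exactly 80% when Φ(5/SD) = 0.80, that is SD = 5/0.8416 = 5.94. P(X ≥ 27) passes one half at an SD of about 12.

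**The case against.** A reader might infer that the rule simply gives the wrong advice. The documents do not support that. At an assumed SD of 15 or more, most trials of equal programs fall in the middle category, and a majority in the top category needs an SD below about 12. No document gives the SD of D. The nearest figure, the prediction error of 16.9 ± 11.6% in the Introduction, is a different quantity, but it does not point towards an SD as small as 5. The row for SD 5 therefore shows the direction of the effect, not a likely value.

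The superiority advice is also worded for a rate of 80% or better. For 27 or more successes the protocol says only that rates below 50% are ruled out. If an observed 80% is required, the problem at the upper anchor is much smaller. The text does not settle which reading applies.

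A reader might further infer that the equivalence trial could succeed only at its type I error rate. That would need the next trial to use the same 5 points as its margin and the mean of D to lie near its median. No margin is stated, and the middle branch also offers the combination approach, which could suit a result where half of the patients do clearly worse on the model program.

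Nor does early stopping add harm. It is pure curtailment: it acts only when the 40-patient category is already fixed.

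Finally, the study is exploratory, and the paired scores will be available when the next trial is planned. All of this limits the size of the problem. None of it re-centres the anchors: Step 2 is independent of the SD, and the direction in Step 3 is certain whenever some differences lie within the tolerance.

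**Conclusion.** The concern holds as a bias in the mapping from success rate to advice. At the middle anchor it is exact for continuous D: a rate of about 50% describes a model program that is 5 points worse in the median patient, and 96% of such trials land in the category linked to an equivalence trial or the combination approach. At the upper anchor the direction is certain but the size depends on an unstated SD and on the reading of the rule. Under normal D with mean 0, equal programs enter the top category in 66% to 11% of trials for SD 10 to 30, or in 9% to 0.6% for SD 10 to 20 if 32 of 40 is required. The sample size, cut-offs, intervals and stopping rule are not in error for the rate itself. This is a conflict between two rules that the article states in full, not a detail left to an analysis plan.

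**What to change.** Keep the primary endpoint, n = 40, the cut-offs, the exact CI and the stopping rule. Change only how the result is turned into advice:

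1. Report three classes with the success rate: model better by more than 5 points, within 5 points, and worse by more than 5 points. Report the tolerance-free paired comparison (D < 0 against D > 0) as well, with a tie rule fixed in advance.
2. State that a high tolerance-based rate alone supports planning a non-inferiority or equivalence trial.
3. Advise a superiority trial only if the tolerance-free comparison, or better by more than 5 against worse by more than 5, also favours the model. Say beforehand what counts as favouring. The three-class version guards against a trivial but consistent gain: with mean D = −1 and SD 1, the tolerance-free rate would be Φ(1) = 84%.
4. State that a rate of about 50% means a median deficit of 5 points on the model program and does not by itself support an equivalence trial.
5. Say whether the superiority advice applies from 27 successes or from an observed 80%.

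The cost is a revised decision paragraph and a short addition to the analysis. No new patients or measurements are needed. The superiority advice becomes somewhat harder to reach, a tie rule is needed, and after an early stop the added comparison rests on fewer than 40 patients.

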#### Statistical analysis

Primary analysis of the primary endpoint: The exact two-sided 95% CI for the success rate will be computed from all patients with defined primary endpoint. In case the study will be stopped with n < 40, confidence limits will also be presented for the virtual scenarios with n = 40 and either success or non-success in all k “remaining” patients where n–k is the actual number of evaluable patients. The purpose of the primary analysis is to obtain advice for the hypothesis of a subsequent larger trial, as described in the sample size section.

For the clinical plausibility, we will examine if there might be differences in quality of life under the two stimulation modalities, and if these differences might be correlated with the measured functional data.

Note on the cross-over design: All analyses will be carried out just with methods for usual paired data. The effects of DBS are largely washed out after 48 h [12, 13] and our measurements will be obtained 4 weeks after a programming change. Therefore, carry over effects should be negligible. However, to rule out any wrong assumptions for the future trial, this study is being planned as a cross-over design, and the possibility of carry-over will be assessed for all endpoints under consideration.

The study database will be validated by the Clinical Trial Center Würzburg (CTCW). Web-based data entry during the study will ensure continuous data transfer to the CTCW. Central data checks and query management will ensure timely delivery and correctness of data. The data will be publically available after publication. ln accordance with the rules of good scientific practice and legal requirements, we will archive our data for at least 10 years.

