**Fig. 2 Fig2:**
[figure not shown]
gives an overview of the examinations per visit. The visits are represented as a row below each other, the respective examinations as marked columns on the right-hand side

During *programming visit*, a DBS expert performs comprehensive reprogramming according to clinical best practices. This represents the usual procedure for initial setting of the stimulator after surgery. This process is described in detail in the section Clinical programming below.

According to *randomization* the unblinded programmer will activate one of the two programs (“*computer” or* “*clinical”*). Adequate measures to keep the patient blinded to the respective settings will be taken (ramp settings > 8 s and patient programmer display reduced to minimal settings). Patients will stay under physician supervision for around 30 min to check for any acute side effects.

*Motor visit 1* is scheduled 4 (± 1) weeks after randomization as the first follow-up. Again, standardized video recordings of the motor examination (TWSTRS/BFMDRS) and patient questionnaires (SF-36, CDQ24) will be taken to evaluate symptom severity and disease-related quality of life. The unblinded DBS programmer will then swap the programs (“*computer” to* “*clinical or* “*clinical” to* “*computer”*). Again, patients will stay under physician supervision for around 30 min to check for any acute side effects and will then be released into the second chronic phase. A telephone safety call 1 week after each change of stimulation parameters was implemented to allow for early response to any problems or suboptimal motor control.

*Motor visit 2* is scheduled 8 (± 1) weeks after randomization as the second follow-up. A third time, standardized video recordings (TWSTRS/BFMDRS) and patient questionnaires (SF-36, CGI) will be taken to evaluate symptom severity and patient’s program preference will be evaluated. The study concludes and the patients can decide which program will be activated for chronic use.

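### Patients who cannot complete the computer-program period have no scoring rule and, as written, leave the denominator, which probably raises the success rate

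*Protocol article*

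**What the plan says.** The Statistical analysis section fixes the primary analysis set: "The exact two-sided 95% CI for the success rate will be computed from all patients with defined primary endpoint". The sample size section counts 40 evaluable participants, not 40 randomised ones.

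Under Outcome measures, for each of the two programs, "we will calculate the symptom severity score after 4 weeks of continuous stimulation, expressed in percent of the pre-operative score". A patient is a success if the computer program is at least as good as the clinical one, with a "tolerance 5% of absolute difference in percentages". The rule compares motor scores only and has no clause for a patient who stops a program.

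Two places anticipate difficulty on a program. The section on image-based prediction says that for each side "one alternative stimulation setting will be proposed, in case the first option leads to otherwise not manageable side effects". The study design section adds a telephone call one week after each change of settings, "to allow for early response to any problems or suboptimal motor control". Neither says how a patient who still cannot continue is scored.

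The Statistical analysis section also plans confidence limits with all remaining patients counted as successes or all as non-successes. These are tied to a study stopped before 40 evaluable patients. They are not stated for randomised patients who have no endpoint.

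**The concern.** The endpoint is meant to record whether treatment on the computer-derived settings succeeds. A patient who cannot stay on those settings because of side effects or poor control has not been treated successfully, yet has no four-week rating and so no value. The exclusion depends on the outcome being estimated. It removes failures and leaves successes untouched, so the remaining proportion rises.

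The two programs also differ in exposure to this risk. The clinical amplitude is set below the individual's adverse-effect threshold. The computer settings come from the model and are then checked by an expert. Loss on the computer side is therefore the more plausible of the two.

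At stake is the choice among three follow-up plans (superiority trial, equivalence or combined approach, further exploratory work). That choice rests on which of 80%, 50% and 20% lie in the interval. The early-stopping counts use the same endpoint values and inherit the same gap.

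**Working it through.** **Inputs.** From the article: 40 evaluable patients; cut-offs of 27 or more, 14 to 26, and 13 or fewer successes; reference rates 80%, 50% and 20%; exact two-sided 95% interval, taken here as Clopper-Pearson. Not in the article: any rate of loss. Values of 0–20% are assumed below.

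**Formula.** For x successes in n, the lower limit is the 2.5% quantile of Beta(x, n−x+1) and the upper limit is the 97.5% quantile of Beta(x+1, n−x).

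**The plan's own figures reproduce.**
- 27/40: 50.9–81.4%, excludes 50%
- 26/40: 48.3–79.4%, excludes 80%
- 14/40: 20.6–51.7%, excludes 20%
- 13/40: 18.6–49.1%, excludes 50%

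The cut-offs are correct for evaluable patients.

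**Adding back excluded computer-period failures.** With d such patients, x/40 becomes x/(40+d).

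| Complete pairs | d | With failures added back | Reading |
|---|---|---|---|
| 27/40 = 67.5% (50.9–81.4) | 1 | 27/41 = 65.9% (49.4–79.9) | changes: 50% back in, 80% out |
| 28/40 = 70.0% (53.5–83.4) | 3 | 28/43 = 65.1% (49.1–79.0) | changes |
| 30/40 = 75.0% (58.8–87.3) | 6 | 30/46 = 65.2% (49.8–78.6) | changes |
| 32/40 = 80.0% (64.4–90.9) | 4 | 32/44 = 72.7% (57.2–85.0) | unchanged: 50% out, 80% in |

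**Expected size.** Let p be the success rate among completers and q the proportion lost because of the computer program. With those patients counted as failures the rate is p(1−q), so the complete-pair rate is too high by p·q. At p = 0.80, q of 5%, 10% and 20% gives 4, 8 and 16 percentage points. At p = 0.80 and q = 10% the rate is 0.80 × 0.90 = 0.72, and the probability of at least 27 successes in 40 is 0.79 instead of 0.98.

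**Losses on the clinical program.** Let c be the proportion lost because of the clinical program, and suppose they would count as successes. The rate over all patients is p(1−q−c) + c, so the complete-pair rate is too high by p·q − c(1−p). This is positive unless c/q exceeds p/(1−p):
- p = 0.675: 0.675/0.325 ≈ 2.1
- p = 0.80: 0.80/0.20 = 4

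One loss of each kind turns 27/40 into 28/42 = 66.7% (50.5–80.4%), and the reading does not change.

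**The case against.** The strongest reply is that the article never says that a patient taken off the computer program is undefined. It states when the value is a success and is silent on stopping. A full protocol or analysis plan could score intolerance as a non-success without contradicting any sentence shown. That is a fair limit on certainty. But the article does state the analysis set, the evaluable-patient count and an endpoint built from ratings on both programs, and together these lead to exclusion unless a further rule is added.

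The safeguards also limit loss. Amplitudes are bounded, an expert checks the settings, an alternative setting lets a patient continue on a model-derived program, and the periods are short. A patient with poor control who attends the visit is rated and can be counted as a failure under the present text. The number affected may therefore be small.

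A reader might infer that the success rate is certainly inflated. The documents do not support that: clinical-program losses are dropped too, and no rate is given for either. A reader might also take the change at 27/40 as typical. It is the most fragile count above the cut-off; at a true rate of 80%, exactly 27 of 40 has probability 0.024. Finally, one might infer that the excluded failures are lost to the planned description of treatment failures, but nothing restricts that description to the primary analysis set.

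**Conclusion.** The point stands in a limited form. As the article is written, patients who cannot complete the computer period for side effects or insufficient control have no endpoint value and leave the primary analysis, although they are failures of the treatment being assessed. The existing best-case and worst-case limits do not reach them.

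Upward bias is probable, not proven. It rests on losses being at least as likely on the computer program as on the clinical one, which the way the two programs are set makes plausible. Its size cannot be stated without a loss rate. Under the assumed 5–20% it is 4 to 16 points at a completer rate of 80%, before any offset. The scenario is sensitive near the cut-off and robust further from it.

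The stronger conclusion, that this defect overturns the trial's result, is not supported. The study is exploratory and its estimate advises the design of a later trial. The change should be made, but the design does not fail without it.

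**What to change.** Add to the Statistical analysis section, and apply in the stopping counts, that every randomised patient who started the computer program and could not complete that period because of side effects or insufficient control has the endpoint value no. These patients then count as evaluable, so n = 40 and the cut-offs of 27, 14 to 26 and 13 remain as they are.

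For all other randomised patients without an endpoint, including those lost on the clinical program, extend the all-success and all-failure limits that the section already plans for remaining patients. Scoring clinical-program losses automatically as successes is not advised, because it would replace the motor comparison with an assumption.

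Keep the complete-pair result as a sensitivity analysis.

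The cost is a few sentences. No clinical rule changes. The success rate may come out slightly less favourable, and the endpoint then includes tolerability as well as motor score, which the text should say openly.
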